## Abstract

**Background:**

The concept of core outcome sets (COS) has been introduced in China for about 10 years. In recent years, some Chinese researchers also committed to developing COS, though the majority of COS are ongoing. However, there were more than 500 published COS for research in the COMET database by 2020. The extent of availability of COS for the top 25 diseases with the highest burden in China is unknown. In addition, the uptake of COS in clinical trials for these diseases is unknown, along with the knowledge, perceptions, and views of the clinical trialist community in China on the use of COS in relation to choosing outcomes for their research.

**Methods:**

The main burden of disease in China will be identified. Then we will search the COMET database to identify if there are ongoing or completed relevant COS research A COS published since 2012 would be preferred to one published before 2012 for the analysis of COS uptake if one meets the eligibility criteria. We will extract scopes of published eligible COS, including condition, population, interventions, and core outcomes. Then we will search the Chinese Clinical Trial Registry using disease names for each disease that has a published COS. We will assess the overlap in scope between clinical trials and COS. Then we will conduct an online survey and semi-structured interviews to identify the knowledge and perceptions of COS among primary investigators of included clinical trials.

**Discussion:**

This research will fill in gaps between COS and the burden of disease in China. Understanding clinical trialists’knowledge and perceptions of COS may help dissemination and application of COS in the future.

**Trial registration:**

This research is registered in Core Outcome Measures in Effectiveness:
https://www.comet-initiative.org/Studies/Details/2563.

## Background

1.

A core outcome set (COS) is an agreed standardized set of outcomes that should be measured and reported, as a minimum, in all clinical trials in specific areas of health or health care.
^
1
^ The concept of COS was introduced in China in 2013.
^
2
^ Chinese researchers have registered more than 80 COS for research in the Core Outcome Measures in Effectiveness Trials (COMET) database by 2022.

A search of the COMET database shows that more than 500 completed COS studies have been published by 2021. The number of COS varies by disease category. The top five disease categories are cancer, rheumatology, neurology, heart and circulation, orthopaedics and trauma.
^
3
^ However, the number of candidates vary by disease category. In addition, there are more than one COS for some conditions, while no COS exists in some other important conditions. Whether there are gaps between COS research and the burden of disease in China remains unclear.

There are some benefits to using COS in clinical trials, which include improving the consistency of outcome reporting, increasing the relevance of outcomes measured to decision-makers, and helping to identify potential selective outcome reporting bias. However, previous research has shown that COS uptake is low in most research areas.
^
4
^
^,^
^
5
^ Research shows that clinical trialists’ awareness and understanding of COS may facilitate the use of COS.
^
6
^ However, Chinese clinical trialists’ awareness, understanding and using of COS are unknown.

The aims of this study are to examine: (1) whether the top 25 diseases with the highest burden in China have relevant COS; (2) the use of COS in clinical trials registered in the Chinese Clinical Trial Registry for these 25 diseases; and (3) views of these clinical trialists on the knowledge, perceptions, and use of COS in relation to choosing outcomes, as well as barriers and facilitators to uptake of COS.

## Methods

2.

### Mapping of burden of disease in China to COS

2.1

**
*2.1.1 Identification of diseases for study*
**

The top 25 causes of disability-adjusted life-years (DALY) in China in 2019 have been identified from the tool of Global Burden of Disease (GBD).
^
7
^ Two researchers (RQ and XF) will also discuss subtypes of disease according to practice guidelines or textbook of internal medicine if necessary. The initial list of diseases for the study is shown in
Table 1.

**Table 1. T1:** The initial list of diseases for the study (ranked by number of disability-adjusted life-years).

Disease category	Burden of disease	Subtypes of disease
Neurology	Stroke	Ischemic stroke, intracerebral hemorrhage, subarachnoid hemorrhage
Heart & circulation	Ischaemic heart disease	Angina pectoris, acute coronary syndrome, myocardial infarction
Lungs & airways	Chronic obstructive pulmonary diseases	/
Cancer	Tracheal, bronchus, and lung cancer	/
Orthopaedics & trauma	Road injuries	/
Ear, nose, & throat	Age-related hearing loss	/
Orthopaedics & trauma	Low back pain	/
Endocrine & metabolic	Diabetes mellitus type 2	Diabetes mellitus type 2
Cancer	Stomach cancer	/
Neurology	Migraine	/
Mental disorders	Depressive disorders	Depression, dysthymia
Orthopaedics & trauma	Falls	
Neonatal	Neonatal disorders	Neonatal preterm birth Neonatal encephalopathy due birth asphyxia and trauma Neonatal sepsis and other neonatal infections Hemolytic disease and other neonatal jaundice Other neonatal disorders
Orthopaedics & trauma	Neck pain	
Cancer	Colon and rectum cancer	Colorectal cancer
Muscle disease	Other musculoskeletal disorders	Exclude: osteoarthritis, rheumatoid arthritis
Neurology	Alzheimer's disease and other dementias	Alzheimer’s disease Dementia
Kidney disease	Chronic kidney disease	Chronic kidney disease due to diabetes mellitus type 1 Chronic kidney disease due to diabetes mellitus type 2 Chronic kidney disease due to hypertension Chronic kidney disease due to glomerulonephritis Chronic kidney disease due to other and unspecified causes
Cancer	Esophageal cancer	/
Heart & circulation	Hypertensive heart disease	/
Cancer	Liver cancer	Liver cancer due to hepatitis B, liver cancer due to hepatitis C, liver cancer due to alcohol use, liver cancer due to NASH, liver cancer due to other causes
Infectious disease	Total burden related to hepatitis B	/
Sense organ diseases	Blindness and vision loss	Glaucoma, cataract, age-related macular degeneration, refraction disorders, near vision loss, other vision loss
Muscle disease	Osteoarthritis	/
Mental disorders	Anxiety disorders	/

**
*2.1.2 Identification of relevant COS*
**

We will manually search the COMET database and identify all COS for diseases/subtypes in the diseases list. We will identify if there are ongoing or completed relevant COS research. The study began on April 7
^th^, 2023 and is ongoing.

**
*2.1.3 Inclusion criteria for COS*
**

(1)The scope appears relevant to a disease in the diseases list;(2)COS for research should have included patient participants;

RQ will identify COS from the COMET database, and XF will check the results. Any discrepancies will be resolved by consensus discussion or by consulting a third reviewer (PW). RQ and PW will discuss all the COS for the 25 causes of DALY and determine which COS are eligible. The criterion related to the inclusion of patient participants follows previous work examining uptake of specific COS, and reflects the impact of patient participation on the choice of core outcomes.
^
8
^

The aim of COS is to promote a single unified approach to evaluating outcomes in a given condition throughout the world, however only 30% of COS published up to the end of 2021 have included participants from anywhere in Asia,
^
8
^ and the majority of COS developed in China are focused on traditional Chinese medicine (TCM). To explore whether the uptake of COS is influenced by whether it was developed by Chinese researchers, we will additionally include a COS published in a Chinese language journal if one meets the inclusion criteria above.

**
*2.1.4 Data extraction*
**

We will describe the number of ongoing and published COS for the highest burden of disease in China. Full texts will be retrieved for published COS only.

Previous COMET systematic reviews, and ongoing inclusion of published COS by COMET, will be used for details of published COS relevant to this work. Data extraction will include the intended use of recommendations, disease category, disease name, population characteristics (age, sex), interventions, geographical locations of COS developers, geographical locations of COS participants will be extracted, and whether patients participated.

**
*2.1.5 Data analysis*
**

Descriptive analysis will be used for general characteristics of COS.

### Exploring uptake of COS in trialists in China

2.2

**
*2.2.1 Identification of clinical trials in the Chinese Clinical Trial Registry*
**

We will search the Chinese Clinical Trial Registry (
https://www.chictr.org.cn/historyversionpub.aspx) according to the disease name extracted for the published COS.

**
*2.2.2 Inclusion and exclusion criteria for clinical trials*
**

**Inclusion criteria for clinical trials:**
(1)Randomised and non-randomised clinical trials;(2)The objectives of clinical trials are for disease therapy;(3)The prospective registration time should be in 2021 and 2022.

**Exclusion criteria for clinical trials:** The clinical trials are to assess the mechanisms of effect of interventions.

If the disease name in the COS is broader, we will further search subtypes of disease. RQ and XF will discuss the list of subtypes of disease, any disagreement will be discussed with a third investigator (HS). XF, WW, ZC, and SL will search for clinical trials from the Chinese Clinical Trial Registry and apply the inclusion and exclusion criteria to identify the eligible clinical trials. RQ will check the results.

**
*2.2.3 Comparison of COS with clinical trials*
**

Inclusion criteria:
(1)An eligible COS exists published since 2012.(2)The number of clinical trials with matching scope to an eligible COS is not less than 40.

A COS published since 2012 would be preferred to one published before 2012 for the analysis of COS uptake if one meets the eligibility criteria. A COS developed by Chinese researchers may be significant for Chinese clinical trialists. If there is an eligible COS developed by Chinese researchers, it will be included. If it does not meet the inclusion criteria for comparison of COS with clinical trials, then the prospective registration time for clinical trials will be expanded.

An online survey will be sent to trialists who registered clinical trials which are relevant to a specific COS. We anticipate a 50% non-response rate, thus if the number of trials is too small, it will be difficult to obtain a reasonable spread of perspectives from trialists about the use of the relevant COS. It was felt that responses from 20 trialists would be helpful based on a typical number of participants involved in qualitative research, thus requiring an anticipated 40 registered trials.

**
*2.2.4 Data extraction and analysis*
**

Data extraction for COS will include: author, title, publication time, condition, population, intervention, outcomes, and outcome measurement instruments (if applicable).

Contact details of trialists (including applicant’s name, the registration contact person’s email and telephone number, the primary investigator’s name, the primary investigator’s email and telephone number) will be extracted, because they will be invited to participate in the online survey. The other data extracted will include: title, the primary investigator’s institutions, study type, disease name, population, intervention, outcomes, and outcome measurement instruments.

For comparing trial outcomes and COS, only published COS will be used. If there are more than two COS for a specific disease, the differences in scope between these COS will be discussed by two reviewers. 

We will compare the overlap in scope between clinical trials and COS according to the framework used in previous research.
^
9
^ The framework is shown in
Table 2.

**Table 2. T2:** The framework for assessing overlap in scope between clinical trials and COS.

		Intervention			
		COS is narrow	Exact match	COS is broader	Different intervention
Population	COS is narrow	A	B	C	D
	Exact match	E	F	G	H
	COS is broader	I	J	K	L
	Different subgroup of the population	M	N	O	P

We will calculate the median percentages of outcomes in each clinical trial that were specific matches, general matches, and non-matches with outcomes in each relevant COS. We will calculate the proportion of outcomes that overlap between the COS and clinical trials for each disease.

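### The registry search widens only downward from the COS disease name, so when a COS is narrower than its Table 1 disease, trials registered only under the parent name have no stated route into the sample

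*Protocol article*

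**What the plan says.** Section 2.2.1 sets the registry search term: the search runs "according to the disease name extracted for the published COS". Section 2.2.2 deals with a mismatch in breadth in one direction: "If the disease name in the COS is broader, we will further search subtypes of disease". The article states no corresponding rule for a COS whose disease name is narrower than the listed disease.

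Narrow COS are foreseen. Section 2.1.2 says that the team will "identify all COS for diseases/subtypes in the diseases list", and Table 1 splits several diseases. For stroke it lists "Ischemic stroke, intracerebral hemorrhage, subarachnoid hemorrhage".

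Two later steps use the retrieved trials. Table 2, titled "The framework for assessing overlap in scope between clinical trials and COS", has a population row (cells A to D) for a COS that is narrower than the trial. Section 2.2.3 admits a COS to the comparison only under this condition: "The number of clinical trials with matching scope to an eligible COS is not less than 40".

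The abstract summarises the search as "using disease names for each disease that has a published COS".

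**The concern.** The search term comes from the COS, and the only stated extension goes towards narrower terms. For a COS on ischemic stroke, the rule as written searches that name. A trial registered simply as stroke is not reached, and two kinds of trial can be lost:

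- Trials that enrol all strokes. These belong in Table 2's row for a narrow COS.
- Trials whose population is exactly the COS population but which are registered under the parent name only.

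The retrieved set feeds the outcome-match percentages, the floor of 40 and the survey mailing list. Selecting trials by the COS's own wording could favour trials already close to that COS, in a study that measures closeness to the COS. A COS near the floor could also be excluded from the uptake comparison because of the search rule and not because trials are few.

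**Working it through.** **1. The plan's own figure.** Section 2.2.3 wants 20 responding trialists and expects 50% non-response: 20 / (1 − 0.5) = 40. The floor is reproduced exactly and is not in dispute. The question is how many trials are retrieved for comparison with it.

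**2. The search rule against the uses of its output.**

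| COS relative to its Table 1 disease | Search stated in 2.2.1 and 2.2.2 | Where a trial registered only under another name stands |
|---|---|---|
| COS is the broader term | COS name plus subtypes | Subtype-named trials are reached |
| COS is the narrower term | COS name only | Parent-named trials have no stated route in |

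Table 2 classifies in both directions, while the search extends in one.

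**3. Where a narrow COS could arise.** Eight of the 25 rows in Table 1 list two or more subtypes: stroke, ischaemic heart disease, depressive disorders, neonatal disorders, dementias, chronic kidney disease, liver cancer, and blindness and vision loss. This shows that the situation is possible. It does not count affected rows, because the article does not say which eligible COS are narrower than their row.

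**4. Effect on the floor (illustration).** Let m be the share of trials that would count as matching but are missed because they carry only the parent name. The article gives no value for m, so every value below is an assumption.

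- True number needed to retrieve 40: 40 / (1 − m), rounded up.
- Number retrieved when exactly 40 exist: 40 × (1 − m).
- Expected responses from those retrieved, at 50% response: 0.5 × 40 × (1 − m).

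| m (assumed) | True number needed | Retrieved of 40 | Expected responses |
|---|---|---|---|
| 0% | 40 | 40 | 20 |
| 5% | 43 | 38 | 19 |
| 10% | 45 | 36 | 18 |
| 20% | 50 | 32 | 16 |
| 30% | 58 | 28 | 14 |
| 40% | 67 | 24 | 12 |
| 50% | 80 | 20 | 10 |

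The effect depends on the true count, which is also unknown. With an assumed 50 matching trials, the floor is missed once m exceeds 20%, since 50 × 0.8 = 40. With an assumed 100, a 40% loss still leaves 100 × 0.6 = 60.

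**5. Which missed trials bear on the floor.** The article does not say which Table 2 cells count as matching scope. If trials broader than the COS do not count, losing them leaves the count unchanged. Trials with exactly the COS population and a matching intervention should count on any reading, and those registered only under the parent name are still missed.

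**The case against.** The strongest reply is that Table 2 is a general grid taken from previous research. It sorts trials once they are found and does not dictate what the search must find. It also has cells for different interventions and different subgroups, which nobody expects to be filled completely. No stated analysis reports counts by row. The exact registry fields and search strings are details that an article may leave to a fuller document, and a hit in a title or population field might retrieve some parent-named trials.

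Much of this stands, and it rules out several stronger readings that a reader might infer:

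- *That the row for a narrow COS will be empty or wholly wrong.* Trials carrying the COS disease name can still be broader in age, sex or other features, and they fall in that row. Only its disease-breadth part is exposed.
- *That the count towards 40 is certainly too low.* Matching scope is undefined, and the number of exact-population trials registered only under a parent name is unknown. Some parent-named trials might also enter through another, broader COS.
- *That at least 8 of 25 diseases are affected.* A row is exposed only if its eligible COS is narrower than the row name.
- *That the abstract describes a different search.* Its one-line summary can be read as the Table 1 disease, but it also fits section 2.2.1, because the disease with a COS can itself be a subtype.
- *That any COS falling short is dropped.* For a COS developed by Chinese researchers that fails the comparison criteria, section 2.2.3 widens the registration window. This softens the floor for that group, though it adds other years and does not recover trials missed in 2021-2022.

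The objection does not remove the core. The article is not silent on breadth: it states a rule, and the rule runs one way.

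**Conclusion.** The point holds as a gap in the search rule. When an eligible COS is narrower than its Table 1 disease, trials registered only under the parent name have no stated route into the sample. The disease-breadth part of Table 2's row for a narrow COS is then under-ascertained, and the count towards the floor of 40 may be too low.

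The size cannot be derived from the article. The shares in the table above are illustrations, and the conclusion does not rest on any one of them. It assumes that at least one eligible COS is narrower than its listed disease, that some relevant trials carry only the parent name, and that the registry search does not pick them up through another field. A tilt towards trials worded like the COS is plausible but not shown. The change is worth making because it is small and the same retrieved set drives the uptake comparison and the survey.

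**What to change.** In sections 2.2.1 and 2.2.2, add that when the COS disease name is narrower than the Table 1 disease, the registry is also searched by the parent disease name. Those records are then screened on population, and scope is assigned with Table 2. Sibling subtypes need not be searched: a COS on ischemic stroke does not call for searches on the two hemorrhagic subtypes. Some Table 1 entries are burden labels and not likely registry terms, such as the entry for other musculoskeletal disorders. For these, the parent term actually used should be written down.

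In section 2.2.3, state which Table 2 cells count as matching scope for the floor of 40.

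The cost is a few sentences of wording and more 2021-2022 records for the same reviewers to screen. Section 2.1.2 describes the study as ongoing, so a supplementary search may still be feasible. The row for a narrow COS would become more complete but not fully so, since trials registered under other umbrella terms could still be missed.

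### The uptake comparison sets no rule that a COS be published before the trial was registered, so trials that pre-date a recent COS count towards its uptake

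*Protocol article*

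**What the plan says.** - **COS eligibility.** Section 2.1.3 sets two criteria, neither of them a date: "The scope appears relevant to a disease in the diseases list" and "COS for research should have included patient participants". Section 2.2.3 adds the only date criterion for the comparison: "An eligible COS exists published since 2012".
- **COS status.** Section 2.2.4 states: "For comparing trial outcomes and COS, only published COS will be used". It does not say published by when.
- **Trial eligibility.** Section 2.2.2 states: "The prospective registration time should be in 2021 and 2022".
- **Timing of the work.** Section 2.1.2 states "The study began on April 7" (the 7th) and continues "2023 and is ongoing". It gives no closing date for COS identification.
- **Floor and expansion.** Section 2.2.3 requires at least 40 scope-matched trials per COS, derived from 20 hoped-for survey responses at 50% non-response. For a COS developed by Chinese researchers that fails the comparison criteria, the registration window is to be expanded. No direction, limit or link to the publication date of the COS is given.
- **Data items.** COS publication time is extracted, but no selection or analysis rule uses it. Beyond contact details, title and institution, the listed trial items are "study type, disease name, population, intervention, outcomes, and outcome measurement instruments". Registration date is not among them.

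**The concern.** Section 2.2.3 describes this comparison as the analysis of COS uptake. Uptake presupposes that the COS was available when the trial's outcomes were registered. In a trial registered earlier, a matching outcome is coincidence or common practice, and a missing one is not a decision against the COS.

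Three things are at stake:

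- The per-trial match percentages for a recent COS mix trials that could have used it with trials that could not.
- The 40-trial floor can be met wholly or partly by trials that pre-date the COS, so it no longer secures the spread of perspectives it was set for.
- Sections 2.3.1.2 and 2.3.2.2 analyse why trialists did or did not use a COS. For a trial that pre-dates the COS, that question has no informative answer about barriers in the registered trial.

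**Working it through.** **1. Is the ordering supplied anywhere?** Each rule that could supply it was checked:

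| Section | Rule | Orders COS before trial? |
|---|---|---|
| 2.1.3 | Scope relevant; patients took part | No |
| 2.2.2 | Trial registered 2021-2022 | No link to COS date |
| 2.2.3 | COS published since 2012 | Lower limit only |
| 2.2.3 | Window expanded for a Chinese-developed COS | No direction, no link to COS date |
| 2.2.4 | COS must be published | No reference to registration |

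None does. The study began after the trial window closed, so a COS published at any point in that window, or between its close and the study's start, satisfies the criteria as written.

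**2. The plan's own figure.** Trials needed = responders / (1 - non-response) = 20 / (1 - 0.5) = 40. This reproduces the stated floor.

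**3. Share of trials that pre-date the COS.** Assumption: registrations are spread evenly over 1 January 2021 to 31 December 2022, which is 730 days. The publication dates are illustrative, because the documents give none.

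- Share pre-dating = days of the window before publication / 730, held between 0 and 1.
- Trials able to use the COS, of 40 = 40 × (1 - share).
- Expected responders from those trials = that number × 0.5.

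| COS published | Days before / 730 | Share pre-dating | Able to use it, of 40 | Responders at 50% |
|---|---|---|---|---|
| By end 2020 | 0 / 730 | 0% | 40 | 20 |
| 1 July 2021 | 181 / 730 | 24.8% (about 25%) | about 30 | about 15 |
| 1 January 2022 | 365 / 730 | 50% | 20 | 10 |
| 1 July 2022 | 546 / 730 | 74.8% (about 75%) | about 10 | about 5 |
| 2023 | 730 / 730 | 100% | 0 | 0 |

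**4. Effect on the planned measure.** Section 2.2.4 plans, for each COS, the median across trials of the percentage of outcomes that match specifically, match generally or do not match, and the overall overlap per disease. Trials that pre-date the COS contribute their background overlap. If publication of the COS raises overlap, mixing them in pulls the summary towards background. Where every trial pre-dates the COS, the summary is background overlap and nothing else. The size of the shift cannot be computed from the documents, because background overlap is unknown and a median does not scale in proportion to the share of such trials.

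**The case against.** Much of the case on the other side stands, and it limits how far the point goes.

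- **Exposure is unknown.** Every COS published from 2012 to 2020 precedes the whole registration window. If all the selected COS fall there, nothing changes unless the window is moved back. This stands.
- **Proportional dilution.** A reader might infer that a true uptake figure shrinks in proportion to the share of trials able to use the COS, for example that 20% full uptake would appear as 10% when half the trials pre-date it. The documents do not support that. Full, partial or no reporting appears only in section 2.3.1.1, to choose the survey version, and the planned measure is a median match percentage whose background value is unlikely to be zero.
- **Chinese-developed COS.** A reader might infer that these are hit hardest because the abstract says most are still ongoing. Ongoing COS cannot enter the comparison, and the abstract does not date those that do.
- **Order cannot be checked.** This would be too strong. COS publication time is extracted, and registration time must be read to apply section 2.2.2. The date is only absent from the listed items, which is weak evidence in a condensed article.
- **Survey invalid.** This would also be too strong. Questions on awareness, willingness to use a COS, use in the next trial and general barriers hold whatever the COS date. The questionnaire is not shown and may ask whether the COS existed at design. Only the reasons tied to the registered trial are exposed.

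One defence does not stand, namely that an article may leave this to a fuller document. The article prints the comparison's inclusion criteria, including a date criterion, and that criterion as stated admits impossible pairs.

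**Conclusion.** The point holds, with a conditional size. As written, section 2.2.3 lets a trial registered before a COS was published count in that COS's uptake analysis and towards its 40-trial floor. For a COS published from mid-2021 to 2023, about 25% to 100% of trials in the window would pre-date it, leaving about 30 down to 0 of 40 able to use it.

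These figures rest on even registration over 2021-2022 and on assumed publication dates. A COS published by the end of 2020 is unaffected unless the window is expanded back past its publication. How many of the selected COS are affected cannot be told from the documents, and no numerical bias in the planned medians can be claimed. It is still worth correcting before the comparison is run, because the rule defines the comparison and both dates needed to repair it are already read.

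**What to change.** Add to section 2.2.3: a COS-trial pair counts towards uptake only if the COS was published before the trial's registration date. Then:

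1. Add registration date to the trial data items in section 2.2.4.
2. Apply the rule before counting trials against the floor of 40.
3. Bind any expansion of the registration window to the same rule.
4. Apply it to survey items on why the COS was or was not used in the registered trial. The other survey and interview questions can stay open to all invited trialists.
5. Report scope-matched trials registered before publication separately, as background overlap.

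A lag between publication and registration, for example 12 months, can be a sensitivity analysis. It should not be the primary rule: the documents give no basis for a particular lag, and it would discard trials that could have used the COS.

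The cost is one eligibility sentence and one recorded field. The downside is that fewer trials count for recent COS, and some COS may fall below 40 and leave the comparison.
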